|                                          | 
NUMBER OF SUBJECTS NEEDED / PHASE II TRIALS / COHORTS H, I and A'
 
 
• Single-arm phase 2 trial based on an optimal two-stage Simon's design
 
• Cohort H: 43 eligible and assessable patients (13 at stage 1) for a total of 47 patients to be included
 
• Cohort I: 29 eligible and assessable patients (13 at stage 1) for a total of 32 patients to be included
 
• Cohort A': 43 eligible and assessable patients (13 at stage 1) for a total of 47 patients to be included
 
                                                                                                                                                                                                                                                                                                                                                                                                                                                                                                                                                                                                                                                                                                                                                                                                                                                                                                                                                                                                                                                                                                                                                                                                                                                                                                                                                                                                                                                                                                                                                                                                                                                                                                                                                                                                                                                                                                                                                                                                                                                                                                                                                                                                                                                                                                                                                                                                                                 |

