|                                      | 
components of treatment must have been received in the same line or as separate lines of therapy
 
 
• A maximum of 1 line of platinum-containing chemotherapy regimen in the metastatic setting, and
 
• A maximum of 1 line of PD(L)1 mAb containing regimen, and
 
• Patients must have received at least 4 months of PD(L1) mAb treatment.
 
 
 
○ No EGFR, ALK, ROS1 positive tumor mutations
 
○ Subjects with known BRAF molecular alterations must have had disease progression after receiving the locally available SoC treatment for the molecular alteration.
 
 
20. For patients with urothelial cancer (cohort J):
 
 
○ A maximum of 1 line of PD(L)1 mAb containing regimen, and
 
○ Patients must have received at least 4 months of PD(L1) mAb treatment.
 
 
21. For HPV-associated cancer (cohort K), TMB-high solid tumors (cohort M) MSI-high solid tumors (cohort N), Non clear-cell renal carcinoma (cohort O):
 
 
○ A maximum of 1 line of PD(L)1 mAb containing regimen, and
 
○ Patients must have received at least 4 months of PD(L1) in the case they received this treatment
 
 
22. For malignant pleural mesothelioma (Cohort P):
 
 
○ A maximum of 1 line of PD(L)1/CTLA-4 mAb containing regimen, and
 
○ Patients must have received at least 4 months of PD(L1)/CTLA-4 mAb treatment in the case they received this treatment
 
 
23. For triple-negative breast cancer patients (Cohort L)
 
 
○ A maximum of 1 line of PD(L)1 mAb containing regimen, and
 
○ Patients must have received at least 4 months of PD(L1) mAb treatment
 
 
Except if CPS<10, an anterior line of PD(L)1 mAb is not mandatory
 
24. For TMB-High cancer patients (Cohort M):
 
 
○ TMB-High is defined as TMB score <math>\geq 16</math> mutations /megabase on tissue or blood sample
 
 |

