#### Secondary endpoints

- Best overall response is defined as the best response across all time points (RECIST v1.1). Following RECIST v1.1 recommendations:
  - The best overall response is determined once all the data for the patient is known.
  - The best overall response will be classified as confirmed complete response (CR), unconfirmed complete response (CRu), confirmed partial response (PR), unconfirmed partial response (PRu), stable disease or progressive disease, as per RECIST v1.1 criteria.
  - As per RECIST v1.1 criteria, to be considered as “confirmed”, complete and partial responses will have to be confirmed at least 4 weeks later to ensure responses identified are not the result of measurement errors.
- Objective response rate at 6 months (6-month ORR) is defined as the proportion of patients with objective response (confirmed or unconfirmed) at 6 months.
- Progression-free status is defined as complete response (confirmed or unconfirmed), partial response (confirmed or unconfirmed) or stable disease more than 24 weeks as defined as per RECIST v1.1 criteria (appendix 3). 6-month progression-free rate (6-month PFR) is defined as the proportion of patients with progression-free status at 6 months. 4-month progression-free rate (4-month PFR) is defined as the proportion of patients with progression-free status at 4 months.
- Growth modulation index (GMI): GMI is defined for each patient as the ratio of its PFS on Regorafenib + Avelumab treatment to its PFS on the previous line of therapy. This method accounts for inter-patient variability, the patient serving as his/her own control and implies by the natural history of the disease that the PFS tends to become shorter in successive lines of therapy. It is thought that an anti-cancer agent should be considered effective if the GMI is greater than 1.3
- Progression-free survival (PFS) is defined as the time from study treatment initiation to the first occurrence of disease progression or death (of any cause), whichever occurs first. 1-year PFS rate and median PFS will be reported.
- Overall Survival (OS) is defined as the time from study treatment initiation to death (of any cause). 1-year OS rate and median OS will be reported.
- Safety profile of the association Regorafenib + Avelumab: Toxicity will be graded using the common toxicity criteria from the NCI v5.0.
- Pharmacodynamic activity:
  - archived tumor tissue will be collected for assessment of the tumor microenvironment.

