### 2.2.2. Phase II trials

Independently for each trial:

- To evaluate the antitumor activity of Regorafenib when prescribed in association with Avelumab in terms of 6-month objective response, 6-month progression-free rate, best overall response, growth modulation index (GMI), 1-year progression-free survival (PFS) and 1-year overall survival (OS).
- To evaluate the Regorafenib safety profile of Regorafenib when prescribed in association with Avelumab.
- To perform pharmacodynamic (PD)/mechanism of action (MOA) biomarkers analysis as well as predictive biomarkers analysis (levels of angiogenic and immunologic biomarkers in blood/tissue at baseline and different study time points).
- For the cohort B: To evaluate the efficacy based on Choi criteria by independent radiologic review

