  13. Women of childbearing potential must have a negative serum pregnancy test within 72 hours prior to receiving the first dose of study medication.
  14. Both women and men must agree to use an highly effective method of contraception throughout the treatment period and for seven months (210 days) in WOCBP or four months (120 days) in men sexually active with WOCBP after discontinuation of treatment. Acceptable methods for contraception are described in section 7.4.1.
  15. Voluntary signed and dated written informed consents prior to any specific study procedure,
  16. Patients with a social security in compliance with the French law.
  17. Documented disease progression (as per RECIST v1.1) before study entry.
    - For patient of cohorts E (STS) and cohort I (Solid tumors - TLS+): this progression will be confirmed by central review on the basis of two CT scan or MRI obtained at less than 6 months in the period of 12 months prior to inclusion.
    - For patient of cohort F (RR-DTC) : this progression will be confirmed by central review on the basis of two CT scan or MRI obtained at less than 12 months prior to inclusion.
  18. Cancelled (MSA6)
  19. For patients with non-small cell lung cancer (cohort H):

- Subjects with histologically or cytologically confirmed diagnosis of non-squamous NSCLC
  - Documented disease progression based on radiographic imaging, during or after a maximum of 2 lines of systemic treatment for locally/regionally advanced recurrent, Stage IIIb/Stage IV or metastatic disease. Two components of treatment must have been received in the same line or as separate lines of therapy
    - A maximum of 1 line of platinum-containing chemotherapy regimen in the metastatic setting, and
    - A maximum of 1 line of PD(L)1 mAb containing regimen, and
    - Patients must have received at least 4 months of PD(L1) mAb treatment.
  - No EGFR, ALK, ROS1 positive tumor mutations
  - Subjects with known BRAF molecular alterations must have had disease progression after receiving the locally available SoC treatment for the molecular alteration.
20. For patients with urothelial cancer (cohort J):
- A maximum of 1 line of PD(L)1 mAb containing regimen, and
  - Patients must have received at least 4 months of PD(L1) mAb treatment.
21. For HPV-associated cancer (cohort K), TMB-high solid tumors (cohort M) MSI-high solid tumors (cohort N), Non clear-cell renal carcinoma (cohort O):
- A maximum of 1 line of PD(L)1 mAb containing regimen, and

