### **9.2.2.Secondary endpoints**

- Best overall response is defined as the best response across all time points (RECIST v1.1). Following RECIST v1.1 recommendations:
  - The best overall response is determined once all the data for the patient is known.
  - The best overall response will be classified as confirmed complete response (CR), unconfirmed complete response (CRu), confirmed partial response (PR), unconfirmed partial response (PRu), stable disease or progressive disease, as per RECIST v1.1 criteria.
  - As per RECIST v1.1 criteria, to be considered as “confirmed”, complete and partial responses will have to be confirmed at least 4 weeks later to ensure responses identified are not the result of measurement errors.
- Objective response rate at 6 months (6-month ORR) is defined as the proportion of patients with objective response (confirmed or unconfirmed) at 6 months.
- Progression-free status is defined as complete response (confirmed or unconfirmed), partial response (confirmed or unconfirmed) or stable disease more than 24 weeks as defined as per RECIST v1.1 criteria (appendix 3). 6-month progression-free rate (6-month PFR) is defined as the proportion of patients with progression-free status at 6 months. 4-month progression-free rate (4-month PFR) is defined as the proportion of patients with progression-free status at 4 months.
- Growth modulation index (GMI): GMI is defined for each patient as the ratio of its PFS on Regorafenib + Avelumab treatment to its PFS on the previous line of therapy. This method accounts for inter-patient variability, the patient serving as his/her own control and implies by the natural history of the disease that the PFS tends to become shorter in successive lines of therapy. It is thought that an anti-cancer agent should be considered effective if the GMI is greater than 1.3
- Progression-free survival (PFS) is defined as the time from study treatment initiation to the first occurrence of disease progression or death (of any cause), whichever occurs first. 1-year PFS rate and median PFS will be reported.

- Overall Survival (OS) is defined as the time from study treatment initiation to death (of any cause). 1-year OS rate and median OS will be reported.
- Safety profile of the association Regorafenib + Avelumab: Toxicity will be graded using the common toxicity criteria from the NCI v5.0.
- Pharmacodynamic activity:
  - archived tumor tissue will be collected for assessment of the tumor microenvironment.

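### The GMI > 1.3 mark is stated for every phase II cohort, but where the previous line was the PD-(L)1 regimen that had to last at least 4 months, the denominator is selected long and GMI is biased downward against that mark

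*Protocol*

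**What the plan says.** GMI is a secondary endpoint of each phase II trial (protocol 2.2.2 and 9.2.2, and the synopsis). It is "the ratio of its PFS on Regorafenib + Avelumab treatment to its PFS on the previous line of therapy". The protocol argues that each patient is his or her own control, and that this "implies by the natural history of the disease that the PFS tends to become shorter in successive lines of therapy". It then gives one reading rule with no cohort caveat: "It is thought that an anti-cancer agent should be considered effective if the GMI is greater than 1.3".

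The inclusion criteria (section 4.1, items 19 to 23) set a minimum duration on one kind of prior therapy:

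- **H and J:** "Patients must have received at least 4 months of PD(L1) mAb treatment", without exception.
- **L:** the same minimum, but a prior PD-(L)1 line is not mandatory if CPS is below 10.
- **K, M, N, O:** the minimum applies only to patients who received PD-(L)1.
- **P:** as for K, with PD-(L)1/CTLA-4.

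These cohorts allow one line of this kind at most. Cohorts A to G and A' exclude prior checkpoint therapy (section 4.2, item 2), so no such minimum acts there.

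**The concern.** Using a patient as his or her own control works only if PFS on the previous line is simply observed. Where a minimum duration of that line is an entry condition, short denominators are removed by design and nothing similar is done to the numerator. The ratio falls even if the treatment changes nothing. This is selection of the denominator; it is a separate matter from censoring of the numerator.

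The practical risk is in how the result is read. The protocol attaches 1.3 to the endpoint as the sign of an effective agent, so a median GMI near or below 1 in H or J could be taken as evidence against the combination when part of the shortfall comes from the eligibility criteria.

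**Working it through.** **Inputs from the protocol.** GMI mark 1.3. Minimum PD-(L)1 duration 4 months. Cohort H: 20% versus 40% 6-month PFR, at least 4 of 13 then at least 13 of 43 (10.1.3). Cohorts J and L: 15% versus 35% 6-month DCR, at least 8 of 28 (10.1.6).

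**Assumptions, because the protocol gives no figure.** PFS is exponential. The previous line is the PD-(L)1 line, and 4 months on treatment stands for 4 months of PFS. For J and L, DCR is read as a 6-month progression-free rate, although its definition counts disease control observed within 24 weeks.

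**1. The design figures reproduce.** By exact binomial calculation, H has one-sided alpha 0.0496 and power 0.800; J/L has alpha 0.0486 and power 0.818. The 40% and 35% rates can therefore be used as the plan's own picture of an active treatment.

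**2. Ceiling on the median GMI.** If every denominator is at least 4 months, each patient's GMI is at most (PFS on study)/4, so the median GMI is at most (median PFS)/4. This does not depend on the correlation between lines. It assumes that the affected patients have on-study PFS at the design alternative. With S(6) = p, the median is 6·ln 2/(−ln p), and GMI > 1.3 requires PFS > 1.3 × 4 = 5.2 months, which has probability p^(5.2/6).

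| Design alternative | Median PFS (months) | Ceiling on median GMI | P(PFS > 5.2 months) |
|---|---|---|---|
| H, p = 0.40 | 4.54 | 4.54/4 = 1.13 | 0.45 |
| J/L, p = 0.35 | 3.96 | 3.96/4 = 0.99 | 0.40 |

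A median GMI of 1.3 with every denominator at exactly 4 months would need a 6-month rate of 0.5^(6/5.2), about 45%.

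**3. Effect of the selection alone.** Take the same exponential median on both lines (3, 4, 6 or 8 months), Gaussian-copula correlation 0, 0.3 or 0.5, and keep only pairs with previous-line PFS of at least 4 months.

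- No change in PFS: median GMI is 0.39 to 0.79, against 1.0 without selection. Between 13% and 29% of patients exceed 1.3, against about 41% to 43% without selection.
- True 1.5-fold prolongation: median GMI is 0.59 to 1.18, against 1.5 without selection.
- 1.76-fold prolongation, which is cohort H's own contrast (ln 0.20/ln 0.40 = 1.76): 0.69 to 1.38. It passes 1.3 in 2 of the 12 scenarios (correlation 0.5, medians 6 and 8 months).

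Closed-form check at correlation 0 and median 3 months: P(GMI > 1.3 | previous PFS ≥ 4) = 0.5^(5.2/3)/2.3 = 0.13.

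**4. When the selection is what moves the median below 1.3.** Apply the cohort H alternative before selection, with correlation 0 and different previous-line medians:

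| Previous-line median (months) | Median GMI, unselected | Median GMI, previous PFS ≥ 4 months |
|---|---|---|
| 2 | 2.27 | 0.70 |
| 3 | 1.51 | 0.59 |
| 4 | 1.14 | 0.52 |
| 6 | 0.76 | 0.42 |
| 8 | 0.57 | 0.35 |

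Selection lowers the median throughout, but it carries it across 1.3 only where the unselected previous-line median is about 2 to 3 months. From about 4 months upward the median is under 1.3 without any selection. With correlation 0.5 and a previous-line median of 2 months, the selected median stays at 1.33. In that case the 40% was applied before selection, so the selected patients do better on study than the design rate; this is why it exceeds the 1.13 ceiling in step 2.

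**The case against.** Five points can be made against the concern.

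- **The PD-(L)1 line need not be the denominator.** This stands. For cohort H, "Two components of treatment must have been received in the same line or as separate lines of therapy", and their order is not fixed. J and L cap the PD-(L)1 lines but not the total, so later lines of other drugs are plausible. The affected share is unknown.
- **Time on treatment is not PFS.** This stands. If treatment stops at progression, PFS is at least as long as treatment, so the 4-month figure is a reasonable proxy but not exact.
- **1.3 decides nothing.** This stands. The sentence is a general remark that does not say whether it applies to a patient, a proportion or a median. Phase II analyses are descriptive (10.3.2.2), and the cohort conclusions rest on 6-month PFR (H) or 6-month DCR (J, L).
- **The simulated sizes depend on the chosen effect.** This stands in part. A 1.5-fold effect stays under 1.3 throughout, but a 1.76-fold effect does not. Equal medians on the two lines also depart from the protocol's premise that PFS shortens from line to line. The ceiling in step 2 needs neither choice.
- **Splitting a descriptive table belongs in the SAP.** A phase II SAP is promised in 10.3 and is not at hand. However, the protocol itself states the 1.3 criterion and states it for every cohort. Correcting a stated criterion is more than asking for absent detail.

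A reader might also infer that cohort L admits only patients with 4 months of PD-(L)1. It does not, because of the CPS exception. Nor is a comparison of GMI with cohorts A to G at risk, since none is planned: each trial is analysed on its own.

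**Conclusion.** The concern holds within limits. For patients in H and J, PD-(L)1-pretreated patients in L (apart from the CPS exception) and pretreated patients in K and M to P, GMI is biased downward against 1.3 when the immediately previous line was the regimen under the 4-month minimum. On exponential PFS, a treatment exactly at the design alternative has a median GMI of at most 1.13 in H and 0.99 in J/L among such patients.

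A reader might infer that any active treatment must fall below 1.3 in these cohorts. The documents do not support that. At the design alternatives, 40% to 45% of patients could still have PFS above 5.2 months; a larger effect can pass 1.3 in some scenarios; and patients whose last line was something else are untouched. Previous-line PFS, the correlation between lines and the affected share are all missing from the protocol, so the overall bias in a cohort's GMI cannot be sized. No primary conclusion, sample size or stopping rule changes.

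**What to change.** In 9.2.2 and the matching synopsis text, add that for cohorts H, J and L, and for pretreated patients of K and M to P, GMI is reported separately by whether the previous line was the PD-(L)1 regimen (PD-(L)1/CTLA-4 in P) subject to the 4-month minimum. State that those patients are not read against 1.3, and keep 1.3 for patients whose previous line carried no minimum duration.

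Prior treatments and time to progression are already recorded at screening (section 5.4), so no new data are needed. The cost is one sentence and one extra row in the GMI table, and fewer patients in these cohorts are read against 1.3. Eligibility, sample size and the primary analysis stay as they are.

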
#### **NUMBER OF SUBJECTS NEEDED / PHASE II TRIALS / COHORTS J to P**

- Single-arm phase 2 trial based on an exact single-stage A'Hern design
- Cohort J / L / N: 28 eligible and assessable patients for a total of 31 patients to be included
- Cohort K / P: 40 eligible and assessable patients for a total of 44 patients to be included
- Cohort M / O: 35 eligible and assessable patients for a total of 39 patients to be included

#### **STATISTICAL ANALYSES**

- Phase I trial (Dose escalation part)
  - All analyses will be descriptive; no p-values will be calculated.
  - Primary endpoint will be analyzed on the population assessable for safety of the phase I trial (escalation part).
  - Toxicity observed at each dose level, graded according to the Common Terminology Criteria for Adverse Events v5.0 from the NCI, will be recorded in terms of event type, severity, dates of beginning and end, reversibility and evolution. Data will be gathered in tables summarizing toxicities and side effects for each dose level and cycle.
  - DLT will be described in terms of number and incidence rates at each dose level. The number and percentage of patients who will have developed a DLT in each dose level will also be reported.
  - Data analyses will be provided by dose groups and for all study patients, combined wherever appropriate.
  - Categorical endpoints: best overall response, ORR under treatment and at 6 months, 6-month ORR and 6-month PFR, will be reported in terms of counts by dose level.
  - Continuous endpoints, e.g. GMI, will be reported in terms of summary statistics that will include number of patients, median, minimum, and maximum, and additional percentiles if appropriate.
  - Survival endpoints (PFS and OS) will be analyzed using the Kaplan-Meier method. The median survival rates will be reported with a 95% confidence interval. Median follow-up will be calculated using the reverse Kaplan-Meier method.
  - Missing data will not be imputed.
- Phase II trials
  - All analyses will be descriptive; no p-values will be calculated.
  - Analyses will be conducted independently for each phase II trial.
  - Analysis of the primary efficacy endpoint will be analysed based on the eligible population assessable for efficacy.
  - Same statistical methods as for the phase I trial.

| Schedule of assessments and procedures                  |               |                             |                 |     |                  |                             |                 |     |                  |                 |                |                            |
|---------------------------------------------------------|---------------|-----------------------------|-----------------|-----|------------------|-----------------------------|-----------------|-----|------------------|-----------------|----------------|----------------------------|
|                                                         | SCREEN
ING | CYCLE 1                     |                 |     |                  | CYCLE 2                     |                 |     |                  | CYCLE N         | DISC. VISIT    | SAFETY FOLLOW-
UP VISIT |
|                                                         |               | Wk1                         | Wk2             | Wk3 | Wk4              | Wk1                         | Wk2             | Wk3 | Wk4              |                 |                |                            |
| Regorafenib (per os)                                    |               | From D1 to D21 continuously |                 |     |                  | From D1 to D21 continuously |                 |     |                  | D1 to D21       |                |                            |
| Avelumab (i.v)Administration during day-hospitalization |               |                             |                 | D15 |                  | D1                          |                 | D15 |                  | D1 + D15        |                |                            |
| Consultation                                            | X             | X                           |                 |     |                  |                             |                 |     |                  |                 | X              | X                          |
| Regorafenib dispensation                                |               | D1                          |                 |     |                  | D1                          |                 |     |                  | D1              |                |                            |
| Day-hospitalization                                     |               |                             |                 | D15 |                  | D1                          |                 | D15 |                  | D1 + D15        |                |                            |
| Written Informed consent                                | X             |                             |                 |     |                  |                             |                 |     |                  |                 |                |                            |
| Demographics data                                       | X             |                             |                 |     |                  |                             |                 |     |                  |                 |                |                            |
| Medical history/baseline condition                      | X             |                             |                 |     |                  |                             |                 |     |                  |                 |                |                            |
| Concomitant treatments                                  | X             | Throughout the study        |                 |     |                  |                             |                 |     |                  |                 |                |                            |
| Physical examination                                    | X             | D1                          |                 | D15 |                  | D1                          |                 | D15 |                  | D1              | X              | X                          |
| Assessment of signs and symptoms                        | X             | Throughout the study        |                 |     |                  |                             |                 |     |                  |                 |                |                            |
| Performance status (ECOG)                               | X             | D1                          |                 | D15 |                  | D1                          |                 | D15 |                  | D1              | X              | X                          |
| Vital signs (heart rate, blood pressure, temperature)   | X             | D1                          |                 | D15 |                  | D1                          |                 | D15 |                  | D1 + D15        | X              | X                          |
| Height                                                  | X             |                             |                 |     |                  |                             |                 |     |                  |                 |                |                            |
| Weight                                                  | X             | D1                          |                 | D15 |                  | D1                          |                 | D15 |                  | D1              | X              | X                          |
| Hematology a                                 | X             | D1                          | D8              | D15 | D22              | D1                          | D8              | D15 | D22              | D1 + D15        | X              | X                          |
| Biochemistry b                               | X             | D1                          | D8 g | D15 | D22 g | D1                          | D8 g | D15 | D22 g | D1 + D15        | X              | X                          |
| Urinalysis c                                 | X             | D1                          |                 | D15 |                  | D1                          |                 | D15 |                  | D1              | X              | X                          |
| Thyroid test h                               | X             | D1                          |                 | D15 |                  | D1                          |                 | D15 |                  | D1              | X              | X                          |
| ECG                                                     | X             | Repeat if indicated         |                 |     |                  |                             |                 |     |                  |                 |                |                            |
| Toxicity                                                |               | Throughout the study        |                 |     |                  |                             |                 |     |                  |                 |                |                            |
| Tumor measurement                                       | X             | Every 8 weeks               |                 |     |                  |                             |                 |     |                  |                 |                |                            |
| Serum pregnancy test (if indicated)                     | X             | X                           |                 |     |                  | D1                          |                 |     |                  | D1              | D1             |                            |
| PK d – phase I                               |               |                             |                 | D15 |                  | D1                          |                 | D15 |                  |                 |                |                            |
| Biomarkers i                                 |               | D1                          |                 |     |                  | D1                          |                 |     |                  | D1 e | D f |                            |
| Stool sample – phase II (optional) j         |               | D1                          |                 |     |                  |                             |                 |     |                  |                 |                |                            |
| Tumor biopsy (optional)                                 | X             |                             |                 |     |                  | D1                          |                 |     |                  |                 |                |                            |

a: differential WBC, haemoglobin, platelets (During treatment : D1, D8, D15 and D22 of cycle 1 and 2, and repeat before each Avelumab injection (ie. Day 1 and Day 15), at discontinuation visit and safety follow-up visit), aPTT, PT, INR (During treatment : D1, D15 of cycle 1 and 2, then D1 of each subsequent cycle, at discontinuation visit and safety follow-up visit)  
b: albumin, alkaline phosphatase, total bilirubin, urea, calcium, chloride, creatinine, creatinine clearance, glucose, LDH, phosphorus, potassium, total protein, SGOT [AST], SGPT [ALT], GGT, sodium, CPK, lipase, amylase (Screening, C1D1 and D15, C2D1 and D15, then D1 of each subsequent cycle, at discontinuation visit and safety follow-up visit)  
c: blood, glucose, protein, gravity (dipstick)  
d: all blood samples will be collected on pre-dose (1 point)  
e: D1C4, D1C6  
f: at progression  
g: only hepatic assessment (AST, ALT, alkaline phosphatase and GGT)  
h: All cohorts :TSH at Screening, on Day 1 and Day 15 of Cycle 1and Cycle 2, then on Day 1 of each subsequent cycle, at discontinuation visit and safety follow-up visit. For cohort F only: Thyroglobulin and Antithyroglobulin antibody at Screening then repeat on Day 1 every 2 cycles, at discontinuation visit and safety follow-up visit.  
i: Biomarkers : Blood samples at C1D1, C2D1, C4D1, C6D1 and at progression (pre-dose).  
j: Stool sample (optional) for the microbiota only at C1D1 (pre-dose)

